**Methods:**

A three-arm, randomized superiority clinical trial with a pre-post and repeated follow-up measures intergroup design using a 1:1:1 allocation ratio will be performed. One hundred and twenty-three cancer survivors with mild to moderate cognitive impairment will be randomly assigned to one of the study interventions: a cognitive rehabilitation intervention group, an intervention group with UP intervention, or a control group on the waiting list. The primary outcome is to observe a significant improvement in cognitive function in both intervention groups and a significant decrease in emotional impairments in comparison with the waitlist group. Improvements in anxiety, depression, and quality of life are also expected as secondary outcomes. These results will be maintained at 6 months of follow-up.

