## Introduction

### Background and rationale {6a}

Breast cancer remains a major health problem worldwide. In 2020, an estimated 2.3 million women were diagnosed with breast cancer and there were 685,000 breast cancer-related deaths globally. With a 5-year prevalence of 7.8 million cases, breast cancer is the most common cancer worldwide. Despite this, advances in treatment and prevention have led to breast cancer survival rates of up to 90%, especially in cancers diagnosed at an early stage [1]. In Spain, a similar pattern can be observed, with breast cancer being one of the most frequently diagnosed types of cancer. In 2020, there were 6651 cases of breast cancer-associated mortality in the country, and it is estimated that the incidence of breast cancer will be 34,750 cases in 2022 [2].

Alterations in cognitive functioning are frequently observed in patients who undergo chemotherapy as treatment for noncentral nervous system cancer. Previous systematic reviews have estimated that up to 75% of patients showed a cognitive decline after chemotherapy, particularly in the domains of memory, executive function, attention, concentration, and processing speed. These symptoms negatively impact on patients’ quality of life, including impairments in terms of autonomy, self-confidence, social relationships, and return to work or education [3–5]. These alterations in cognitive functioning are usually mild to moderate and frequently appear after chemotherapy. However, the persistence of these symptoms varies over time. For example, according to several studies, 15–35% of patients report experiencing changes in their cognitive functioning months after the end of treatment [3]. In breast cancer patients, these alterations are observed to appear after chemotherapy and continue to be present 1, 5, and even 20 years after treatment [4]. In this line, Wefel et al. [6] found that 71% of breast cancer patients showed cognitive impairment after chemotherapy, and 61% of patients showed cognitive impairment 6 months after completing treatment. These results are similar to those of Collins et al. [7], who observed cognitive impairment in 48% of breast cancer patients and found that more than a third continued to show this impairment 1 year after treatment. Despite these results, few studies have examined the long-term cognitive decline in patients, although evidence suggests an improvement in cognitive decline after 6 months of chemotherapy completion [5].

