### Objectives {7}

The following research hypotheses have been formulated:The UP will be more effective in reducing cognitive impairment, symptoms of anxiety, depression, and quality of life than the neuropsychological treatment at post-treatment and follow-up (6 months).Patients in the UP and in the neuropsychological treatment group will obtain better scores in cognitive impairment and symptoms of anxiety, depression, and quality of life than those in the waitlist group at post-treatment and follow-up (6 months).

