### Outcomes {12}

#### Primary outcomes

Participants are expected to show an improvement in cognitive performance (FACT-COG, MFE-30, HVLT-R, TMT, and COWAT) following both interventions (UP and neuropsychological treatment) in the post-treatment (T1) with respect to the pre-treatment (T0). These positive changes are expected to remain stable for 6 months in follow-up (T2), but the participants in the UP intervention group are expected to obtain better scores than the cognitive neuropsychological intervention group. Therefore, better scores are expected in cognitive performance measures for the variables assigned to each test. Thus, no significant improvement in the waitlist control group is expected either at T1 compared to T0, or at T2 compared to T1. On the other hand, there is no broad statistical agreement about the cut-off for a clinically significant change in cognitive impairment [23]. In a longitudinal study, Hermelink et al. [23] considered that a change in cognitive impairment of 1 standard deviation (SD) from the norm indicates mild impairment and a change of 2 SD moderate impairment. Thus, the present study considers 1 SD and 2 SD from the mean in the score of each cognitive measure for T1 or T2 with respect to the initial measurement of each test (T0) as slight and moderate significant changes, respectively

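### The primary outcome on cognition is worded as within-arm improvement from T0 to T1, while the hypothesis, the sample-size rationale and the main planned analysis are between-arm

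*Protocol article*

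**What the plan says.** The primary outcome is defined in the protocol article under Outcomes {12}, Primary outcomes. It names five cognitive measures (FACT-Cog, MFE-30, HVLT-R, TMT, COWAT) and expects improvement "following both interventions (UP and neuropsychological treatment) in the post-treatment (T1) with respect to the pre-treatment (T0"). For the control arm it says that "no significant improvement in the waitlist control group is expected either at T1 compared to T0, or at T2 compared to T1". Its thresholds for slight and moderate change (1 SD and 2 SD) also refer back to each test's own T0. The only between-arm statement in the section concerns the two active arms: "the participants in the UP intervention group are expected to obtain better scores than the cognitive neuropsychological intervention group". It states no difference between an active arm and the waitlist.

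The Methods part of the abstract expects significant cognitive improvement in both intervention groups and then "a significant decrease in emotional impairments in comparison with the waitlist group". The waitlist comparison clearly belongs to the emotional part. Whether it also covers cognition is unclear.

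Other sections are between-arm:
- Objectives {7}, hypothesis 2: patients in both active arms "will obtain better scores in cognitive impairment and symptoms of anxiety, depression, and quality of life than those in the waitlist group", at post-treatment and at 6 months.
- Sample size {14}: d = 0.5 is assumed for differences between the interventions and the waitlist.
- Statistical methods {20a}: mixed linear models cover change over time and between-group differences. The comparisons of the active arms with control, and with each other, are ranked as most important.

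**The concern.** A significant change in one arm beside a non-significant change in another is not evidence that the arms differ. The pattern also depends on anything that moves all arms together, and the document gives reasons to expect such a shift. The Background says that "evidence suggests an improvement in cognitive decline after 6 months of chemotherapy completion", and the exclusion list admits patients from 6 months after their last chemotherapy. All arms, including the waitlist, take every assessment, and T0 and T1 are separated by an 8-week intervention. HVLT-R, TMT and COWAT are performance tests, on which some gain from repetition is plausible.

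Two misreadings follow. A shared gain could be reported as primary success of an active arm. Equally, a treatment that works could seem to miss its primary outcome because the waitlist also improved significantly. The randomised waitlist exists to remove the shared course, and the primary outcome wording does not use it for that. With two different contrasts on paper, the choice between them could also be made after results are known.

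**Working it through.** **The plan's own figure.** The stated sample size reproduces as a repeated-measures ANOVA, between factors, with f = 0.25, 3 groups, m = 3 measurements, correlation 0.5 and alpha 0.05. The noncentrality is f²·N·m / (1 + (m − 1)·0.5) = 0.0625 × 108 × 3 / 2 = 10.125, which gives power 0.809. N = 108 is the smallest balanced total reaching 0.80. Then 108 × 1.13 = 122.04, rounded up to the stated 123. So the sizing test is itself between-arm. No sample-size figure is challenged here.

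**Inputs for the illustration.** From Sample size {14}: 36 per arm, correlation 0.5, effect 0.5 SD. Assumed: equal SD at both visits, two-sided 0.05, and a shared T0-T1 gain c of 0.2, 0.3 or 0.4 SD in every arm.

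**Within-arm test.** The SD of change is √(2(1 − 0.5)) = 1 SD. The paired t statistic has noncentrality c·√36 = 6c on 35 df. Let p be the chance that an arm with gain c shows a significant improvement, and q the same for an arm with gain c + 0.5. The arms are independent, so:
- no treatment effect: P(both active arms significant, waitlist not) = p²(1 − p)
- true effect of 0.5 SD in both active arms: P(same pattern) = q²(1 − p)

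| c (SD) | p | q | no effect: p²(1 − p) | true effect: q²(1 − p) |
|---|---|---|---|---|
| 0.2 | 0.214 | 0.983 | 0.036 | 0.760 |
| 0.3 | 0.417 | 0.997 | 0.101 | 0.579 |
| 0.4 | 0.646 | 0.999 | 0.148 | 0.354 |

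The function p²(1 − p) peaks at p = 2/3 with value 4/27 = 0.148, so the no-effect pattern cannot exceed about 15% per measure. Beyond c of about 0.4 it falls, because the waitlist becomes significant too (11.7% at 0.5 SD, 5.4% at 0.6 SD). Under a true effect the pattern keeps fading, to 17% at 0.5 SD and 6% at 0.6 SD. At c = 0 the figures are 0.1% and 67%. A simulation of 40,000 trials agrees (for example 14.7% and 35.4% at c = 0.4).

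**Between-arm contrast.** The expected difference in change is (c + δ) − c = δ, where δ is the treatment effect, so c cancels. In simulation the chance of a false result favouring treatment was 2.4% to 2.6% per contrast at shared gains between 0 and 0.6 SD. Power at δ = 0.5 is about 56% per contrast on change scores, or 69% with baseline adjustment, whatever the value of c.

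The between-arm contrast is therefore not always the likelier to succeed. At c = 0.2 the within-arm pattern appears more often (76%). Its advantage is that it tests the stated hypothesis and does not move with the shared gain.

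**The case against.** The strongest reply is that the section describes what is expected and sets no decision rule. It does not attach the word significant to the active arms' T0-T1 gain, and no paired test is planned anywhere. The trial is called a superiority trial with an intergroup design, it is sized on differences from the waitlist, and the statistical methods put the between-arm comparisons first. All of this stands.

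A reader might infer that the trial will be judged by comparing within-arm p-values, or that it lacks a between-arm analysis. The documents support neither reading. The defect is in the primary outcome wording and not in the analysis.

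A reader might also quote larger no-effect rates: 17-24% for one given active arm significant with the waitlist not, or 30-39% for at least one active arm. These are correct for those looser patterns at 0.2 to 0.4 SD. The section names both interventions, however, so the matching figures are 3.6% to 14.8%.

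The size of the shared gain is also open. The Background reports impairment persisting for years as well as recovery, and the exclusion list admits patients up to 6 years after chemotherapy (the inclusion wording on this differs). Two of the five measures are questionnaires, for which the retest argument is weaker. This limits how far the percentages can be pressed. It does not remove the mismatch between the outcome wording and hypothesis 2.

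**Conclusion.** The point holds as a wording defect of moderate severity. The section that defines the primary outcome describes within-arm change on cognition and gives no active-minus-waitlist difference, and the abstract does not clearly supply one. Hypothesis 2, the sample-size rationale and the leading planned comparison all need that difference. The mixed model can deliver it.

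The more serious side is a working treatment missing the expected pattern: at shared gains of 0.3 to 0.4 SD this happens in about 42% to 65% of trials (1 − 0.579 and 1 − 0.354). A false appearance of the pattern is limited to about 15% per measure. Both figures rest on an assumed shared gain, 36 analysed per arm, correlation 0.5 and equal SDs. They describe the pattern as worded, not the error rates of the planned model.

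**What to change.** Reword the opening of Primary outcomes along these lines: *The primary outcome is the between-arm difference in change from T0 to T1 on the cognitive measures (each active arm minus waitlist; UP minus neuropsychological treatment), estimated from the mixed linear model in the statistical methods.* Remove from the primary outcome the expectation that the waitlist will show no significant improvement. Bring the abstract's primary outcome sentence into line, and report within-arm T0-T1 changes as descriptive only. Settle this before results are seen.

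The cost is a change of wording. It needs no new patients, data or model. The downside is that favourable within-arm changes can no longer be presented as the primary result.

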#### Secondary outcomes

The secondary outcomes include changes in the level of QoL, anxiety, and depressive symptoms (QLQ C-30, BR23, and HADS) of the participants in both intervention groups, with better scores for the UP intervention group. Therefore, changes are expected in T1 with respect to T0 in the mean for QLQ C-30, BR23, and HADS scores and are expected to persist in T2. These scores are expected to remain stable in the waitlist group. The expected changes are manifested by a decrease in the score for each scale. Zwerenz et al. [24] used the HAD scale, specifically the depression subscale (HADD), to measure depressive symptoms and considered a variation of at least two points in the different measures as a clinically significant change in symptoms. Therefore, this study assumes that a variation of at least two points from the mean on the anxiety (HADA) and depression (HADD) subtests indicates a clinically significant change in symptom intensity. According to various authors, a change in QLQ C-30 scores of 5 to 10 can be considered as “little” change in terms of quality of life and of 10 to 20 as “moderate” change, while if this variation is greater than 20, the change is “very much” and a change of 10 points is considered meaningful [25, 26]. Thus, this study considers that a variation of 5–10 points, 10–20 points, and more than 20 points from the mean are considered as slight, moderate, and high significant changes, respectively.

### Participant timeline {13}

The schedule for recruitment, interventions, assessment, and follow-up are shown in Fig. 2.

**Fig. 2 Fig2:**
[figure not shown]
Schedule of enrolment, interventions, and assessments

### Sample size {14}

The sample size has been estimated based on data obtained in a similar randomized trial with cancer patients of different types [12]. This study examined the effect of a cognitive rehabilitation program on cognitive impairment compared to a control group. The results showed a moderate effect size of 0.49 at post-treatment. Given these results, a medium effect size of 0.5 (*d* index) has been assumed to detect differences between the interventions and the waitlist group. Because no software was available to determine the sample size for linear mixed model analyses, we used the *f* index of G*Power. Therefore, an effect size of 0.25 (*f* index) is assumed, equivalent to *d* = 0.5. Thus, with a statistical power of 0.80, an alpha level of 0.05, a correlation between repeated measures of 0.5 and three groups, a total sample of 108 participants (36 participants in each group) is required. Previous studies have reported a participant withdrawal rate of around 13% [12]. Therefore, assuming this withdrawal rate, the total sample would be 123 participants, 41 per group.

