### Trial design {8}

This is the protocol of a three-arm, controlled, randomized superiority trial, with a pre-post and repeated follow-up measures intergroup design. Participants with mild to moderate cognitive impairment will be randomly assigned to group 1: Unified Protocol for Transdiagnostic Treatment of Emotional Disorders (UP) intervention, group 2: Neuropsychological intervention, or group 3: Waitlist control group. For ethical reasons, the participants in group 3 will be offered the option to receive the neuropsychological intervention. The evaluation will be carried out at three time points: an initial evaluation prior to randomization (pre-treatment; T0), at the end of the intervention (post-treatment; T1), and at 6 months after completing the intervention (T2) (see Fig. 1).

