## Assignment of interventions: allocation

### Sequence generation {16a}

Participants who obtain scores indicating mild or moderate cognitive deterioration will be randomly assigned to one of the three interventions (Neuropsychological treatment/Unified Protocol for the Transdiagnostic Treatment of Emotional Disorders (UP)/waitlist group) at a 1:1:1 ratio using a computer-generated set of numbers (https://www.randomizer.org/) and stratified by psychiatric medication and fibromyalgia diagnosis (if any).

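### The sample size converts d = 0.5 to f = 0.25 with the two-group rule in a three-group design; on a literal reading of the assumption, power at 108 is about 76%, not 80%

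*Protocol article*

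**What the plan says.** The Sample size {14} section starts from an earlier trial of cognitive rehabilitation against control: "The results showed a moderate effect size of 0.49 at post-treatment". From this, "a medium effect size of 0.5 (*d* index) has been assumed to detect differences between the interventions and the waitlist group". It then explains the choice of tool: "Because no software was available to determine the sample size for linear mixed model analyses, we used the *f* index of G*Power". The conversion follows: "Therefore, an effect size of 0.25 (*f* index) is assumed, equivalent to *d* = 0.5". The other inputs are "with a statistical power of 0.80, an alpha level of 0.05, a correlation between repeated measures of 0.5 and three groups", and the result is 108 participants, 36 per group. Allowing for 13% withdrawal, the total becomes 123, or 41 per group.

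Two design facts enter the calculation. Trial design {8} says "The evaluation will be carried out at three time points": T0 before randomisation, T1 at the end of treatment and T2 six months later. Sequence generation {16a} sets allocation "at a 1:1:1 ratio using a computer-generated set of numbers".

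**The concern.** Cohen's f is the standard deviation of the group means divided by the within-group SD. With two equal groups this equals d/2, which is where 0.25 comes from. With three equal groups it depends on where all three means lie, and d/2 is no longer the general answer. The section enters three groups into the software but takes f from the two-group rule, so the f it uses is not the one its stated d implies.

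The stated power, the 108 and the 123 all rest on that f. If the f implied by the stated assumption is smaller, 108 completers do not give the stated 80% for the test that was run, and part of the withdrawal allowance is needed before anyone withdraws.

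**Working it through.** **Inputs.** d = 0.5, f = 0.25, alpha 0.05, power 0.80, correlation r = 0.5, k = 3 groups, N = 108 and 13% withdrawal come from Sample size {14}. The m = 3 measurements come from Trial design {8}, and equal allocation from Sequence generation {16a}.

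**Which test gives 108?** The section does not name it. At f = 0.25 and r = 0.5, the smallest N for 80% power is:

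| Test | N |
|---|---|
| Between factors, 3 groups, m = 3 | **108** |
| Between factors, 3 groups, m = 2 | 120 |
| Between factors, 3 groups, m = 4 | 102 |
| Within factors, m = 3 | 30 |
| Within-between interaction, m = 3 | 36 |
| One-way ANOVA, 3 groups | 159 |
| Between factors, 2 groups, m = 3 | 86 |

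Only the first returns 108. It is used below as an inference.

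**Formula.** Noncentral F with df = k − 1 and N − k, and

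λ = f² × N × m / (1 + (m − 1)r).

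With m = 3 and r = 0.5, m / (1 + (m − 1)r) = 3/2 = 1.5.

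**The plan's own figure.** f = 0.25, N = 108: λ = 0.0625 × 108 × 1.5 = 10.125, power 80.9%. N = 105 gives 79.7%, so 108 is the first multiple of three to reach 80%. The printed figure is reproduced.

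**f from the stated d.** With means 0, 0.5 and 0.5, the grand mean is 1/3 and

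f² = [(1/3)² + (1/6)² + (1/6)²] / 3 = (1/6)/3 = 1/18, so f = 0.5 × √2/3 = 0.236.

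**Power at that f.**
- N = 108: λ = (1/18) × 108 × 1.5 = 9.0, power 75.8%.
- N = 120: λ = 10.0, power 80.5%. This is the first multiple of three to reach 80%, 12 above 108.
- N = 123, if nobody withdrew: λ = 10.25, power 81.5%. With 13% withdrawal, 123 × 0.87 = 107 remain.

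**What f = 0.25 means in this pattern.** d = 0.25 × 3/√2 = 0.53 in both active arms.

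**Sensitivity to the pattern of means, N = 108.**

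| Means (waitlist, then the two active arms) | f | Power |
|---|---|---|
| 0, 0.5, 0.5 | 0.236 | 75.8% |
| 0, 0.4, 0.6 | 0.249 | 80.7% |
| 0, 0.5, 0.6 | 0.262 | 84.7% |

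**Sensitivity to when the gap exists.** This test compares group means averaged over T0, T1 and T2. If both active arms are 0.5 above waitlist at T1 and T2 but equal to it at T0, the averaged gap is (0 + 0.5 + 0.5)/3 = 0.333. Then f = 0.333 × √2/3 = 0.157, λ = 4.0, and power at 108 is about 41%.

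**The case against.** The strongest reply is that the document never says the active arms are equal. It expects the Unified Protocol (UP) arm to do better than the neuropsychological arm (Objectives {7}, Outcomes {12}), and the 0.49 behind d comes from rehabilitation, which most resembles the neuropsychological arm. On that view, 0.5 for neuropsychological treatment and a little more for UP would bring f to 0.25 or above. This stands in part: the 76% is conditional on equal arms and cannot be stated flatly. It does not rescue the text, because the section gives one d for both interventions, states no larger effect for UP, and derives f from d by an equivalence that fails with three groups.

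A second reply is that the test is inferred and that 76% is itself not the power of the planned mixed-model comparisons. Both points are right. Averaging over a pre-randomisation visit moves the answer far more than the conversion does, so any restated figure must say what it is averaged over. The false equivalence does not depend on which test was used.

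Third, the gap is small: d = 0.53 against 0.50, and the 120 needed is below the planned 123. That is also right, and it is why no increase in N is asked for.

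A reader might infer something worse: that 0.5 is the gap between the best arm and waitlist, with the other active arm midway, giving f = 0.204 and much lower power. The documents do not support this. They take 0.5 from a rehabilitation programme, so giving the neuropsychological arm only 0.25 would halve the effect from which d was drawn.

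**Conclusion.** The concern holds in a conditional form. The stated equivalence of f = 0.25 and d = 0.5 is wrong for three equal groups, and the stated N and power do not follow from the stated d. On the literal reading, with both interventions 0.5 SD above waitlist, power at 108 is about 76% instead of 80%, and 80% needs 120 completers.

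This rests on three assumptions: that the test is the one that reproduces 108, that the active arms are equal, and that the 0.5 gap applies to the mean over all three measurements. Relaxing the second can restore 80%; relaxing the third, so that the gap is present only at T1 and T2, lowers power to about 41%. It would go too far to conclude that the trial as planned has 76% power for its main comparisons, since neither the test nor the pattern of means is stated. It is a modest error in a figure that the trial relies on, and it should be corrected.

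**What to change.** In Sample size {14}:

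1. Delete the statement that f = 0.25 is equivalent to d = 0.5.
2. Name the G\*Power test and the number of measurements.
3. State the three assumed means, say that they are averages over the measurements, and give their own f (0.236 for 0, 0.5, 0.5).
4. Keep N = 123, and then either restate power as about 76% at 108 completers for those means, or keep 80% and say that it applies to about d = 0.53 in both active arms on the same averaged basis.

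The cost is one or two sentences and a slightly less favourable stated figure. No participants are added, and the design and analysis do not change.

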## Statistical methods

### Statistical methods for primary and secondary outcomes {20a}

The obtained data will be analyzed following the intention-to-treat (all randomized patients are included in the analysis) and per protocol (only patients with post-treatment assessment are included in the analyses) approaches. In an intention-to-treat analysis, incomplete or missing data will be considered using the maximum likelihood estimation method. First, ANOVA or chi-square tests will be performed to compare the demographic variables and outcome measures at baseline (T0). Second, to examine longitudinal changes over time (baseline, post-treatment, and follow-up) and between-group differences in the mentioned variables, mixed linear models will be used, since these models are more precise than repeated measures ANOVA [41]. The Friedman test will be performed to analyze a potential group-level effect among participants receiving the intervention together. In addition, Cohen’s *d* with bias corrections will be calculated to determine the effect size of the between-group comparisons. The most important analysis will be performed between the two active groups (the neuropsychological treatment group and the transdiagnostic treatment group) and the control group, as well as a comparison between both active groups to observe the evolution of cognitive deficits, anxiety-depressive symptoms, and quality of life of the participants just after the application of the interventions and at 6 months of follow-up. Once the analyses are performed, summary tables will be provided for all the planned evaluations: baseline (T0), end of treatment (T1), and follow-up at 6 months (T2). The results will be presented in the form of frequency tables and by means of descriptive statistics (the mean, standard deviation, and percentages) to summarize the characteristics of both the total sample and the participants in each of the three groups. Finally, the results of the study will be reported in accordance with the 2010 statement of the Consolidated Standards of Reporting Trials (CONSORT) [42] and the 2013 guidelines for Standard Protocol Items: Recommendations for Interventional Trials (SPIRIT) [43].

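### The 80% power claimed for 108 participants belongs to an omnibus group effect averaged over all visits; one active arm versus waitlist at T1 has about 55–68%

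*Protocol article*

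**What the plan says.** Sample size {14} starts from a trial of cognitive rehabilitation against control: "The results showed a moderate effect size of 0.49 at post-treatment". A medium effect of d = 0.5 "has been assumed to detect differences between the interventions and the waitlist group". The section says that no software was available for linear mixed models, so G*Power was used with the f index: "an effect size of 0.25 (*f* index) is assumed, equivalent to *d* = 0.5". The calculation was made "with a statistical power of 0.80, an alpha level of 0.05, a correlation between repeated measures of 0.5 and three groups", giving 108 in total, 36 per group. With withdrawal of around 13%, "assuming this withdrawal rate, the total sample would be 123 participants, 41 per group". The G*Power routine, the number of measurements, the contrast and the visit are not named.

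Trial design {8} sets three assessments, with T0 before randomization. Objectives {7} gives two hypotheses, each for post-treatment and for 6 months. The first sets UP against neuropsychological treatment ("The UP will be more effective in reducing cognitive impairment"); the second sets the two active groups against the waitlist. Statistical methods {20a} plans mixed linear models and states: "The most important analysis will be performed between the two active groups" and the control group, with a comparison of the two active groups in addition, just after treatment and at 6 months.

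**The concern.** A power statement applies to one test. The inputs given here lead to a test that is not among the comparisons listed in Objectives {7} or Statistical methods {20a}. If 80% is then read as the power of each arm comparison, a non-significant result will be taken as stronger evidence of no effect than it is. This matters most for the first hypothesis, which compares two active treatments and for which no effect size was set. The Discussion also presents the sample size estimate as a strength of the trial, so the figure will be relied on.

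**Working it through.** **Inputs from the protocol.** f = 0.25, d = 0.5, power 0.80, alpha 0.05, correlation r = 0.5, k = 3 groups, N = 108 (36 per arm), inflated to 123 (41 per arm) for 13% withdrawal: Sample size {14}. Measurements m = 3, with T0 before randomization: Trial design {8}. Two-sided tests are assumed for pairs of arms, since sidedness is not stated.

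**1. Reproducing 108.** For the repeated-measures between-factors test, λ = N f² m / [1 + (m − 1) r], with df = (k − 1, N − k).
- N = 108: λ = 108 × 0.0625 × 3/2 = 10.125, df 2 and 105, power 0.809.
- N = 105: power 0.797.

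So 108 is the smallest total with equal arms that reaches 80%. The other standard routines give different totals at the same inputs:

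| Routine | N |
|---|---|
| Between factors, m = 2 | 120 |
| Within-between interaction, m = 3 / m = 2 | 36 / 42 |
| Within factors, m = 3 / m = 2 | 30 / 36 |
| One-way ANOVA | 159 |

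**2. Converting d to f.** f is the standard deviation of the group means divided by the within-group SD. It equals d/2 for two equal groups. With three arms and a largest difference of 0.5:
- means (0.5, 0.5, 0): f = 0.236;
- means (0.5, 0.25, 0): f = 0.204.

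**3. The sized test with the correct f, and with no effect at T0.** Arms do not differ in expectation before randomization. If the effect is present only at T1 and T2, the three-visit average is 2/3 of it, so λ is multiplied by 4/9.

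| f | λ | Power, same effect at all 3 visits | λ × 4/9 | Power, no effect at T0 |
|---|---|---|---|---|
| 0.25 | 10.125 | 0.809 | 4.5 | 0.45 |
| 0.236 | 9.0 | 0.76 | 4.0 | 0.41 |
| 0.204 | 6.75 | 0.625 | 3.0 | 0.31 |

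**4. One active arm versus waitlist at T1, d = 0.5.** Noncentral t with noncentrality d √(n/2). Baseline adjustment with r = 0.5 reduces the residual SD to √(1 − 0.25) = 0.866, so d becomes 0.5/0.866 = 0.577.

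| Case | Unadjusted | Baseline-adjusted |
|---|---|---|
| 36 per arm, alpha 0.05 | 0.55 (noncentrality 2.12) | 0.68 (noncentrality 2.45) |
| 41 per arm, alpha 0.05 | 0.61 | 0.73 |
| 36 per arm, alpha 0.025 (two contrasts) | 0.44 | 0.57 |

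With 36 per arm, the difference detectable with 80% power is d = 0.67 unadjusted or d = 0.58 baseline-adjusted.

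**5. Pooled active arms versus waitlist at T1, d = 0.5, 72 against 36.** The noncentrality is d √(72 × 36/108) = d √24. Power is 0.68 unadjusted and 0.80 baseline-adjusted; with 82 against 41, the adjusted power is 0.85.

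**6. UP versus neuropsychological treatment.** The protocol gives no effect size. Taking d = 0.2 to 0.3 purely as an assumption, T1 power with 36 per arm is 0.13 to 0.24 unadjusted and 0.16 to 0.31 baseline-adjusted.

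**7. Withdrawal.** 108 × 1.13 = 122.0, which becomes 123 in three equal arms. Allowing for a 13% loss means dividing: 108/0.87 = 124.1. Conversely, 123 × 0.87 = 107.0.

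**The case against.** A reader might infer that the trial lacks 80% power for every contrast it will interpret. The protocol does not support that. Statistical methods {20a} can be read to include the two active groups together against the control group, and that contrast reaches 0.80 at T1 with baseline adjustment (step 5). A baseline-adjusted comparison of one active arm with waitlist on the mean of T1 and T2 would have 0.84 with 36 per arm, if d = 0.5 held at both visits. However, the cited effect is post-treatment only, and the plan looks at the two times rather than their average. Objectives {7} also reads naturally as arm by arm, so the pooled reading is possible but is not fixed.

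Three further objections have weight. The G*Power routine is inferred, although the match is exact and unique among the routines tried. The section openly calls its method a substitute for a mixed-model calculation; that explains the approximation, but not its aim at a different effect or the incorrect conversion of d to f. And 55–68% assumes 36 contributing per arm and one unsplit alpha. Under the planned maximum likelihood analysis, participants with partial data contribute, so the figure can rise towards 61–73%, which is still below 80%.

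The withdrawal shortfall is about one participant, on a rate given only as approximate. It carries no weight here.

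**Conclusion.** The concern holds for the arm-by-arm comparisons at a single visit. The stated 80% is not delivered for one active arm versus waitlist at T1: power is about 0.55 to 0.68 with 36 per arm, or 0.61 to 0.73 with 41, and 0.44 to 0.57 with 36 if alpha is split over two contrasts. These figures rest on d = 0.5, r = 0.5 and two-sided tests. At T1, only pooled active arms versus waitlist with baseline adjustment comes to about 0.80 with 36 per arm.

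The equivalence of f = 0.25 and d = 0.5 is wrong for three arms whichever routine was used. For UP versus neuropsychological treatment, what stands is that no effect size was set; the low power in step 6 depends on an assumed effect and is illustrative only.

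**What to change.** Reword Sample size {14}; no more patients are needed.

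- Name the contrast and visit to which the power applies, and restate it. For one active arm versus waitlist at T1, baseline-adjusted, 36 per arm gives about 68% power at d = 0.5, or 80% at d = 0.58. If pooled active arms versus waitlist is meant, say so; about 80% then holds with baseline adjustment. Which contrast leads is the sponsor's choice.
- Delete the statement that f = 0.25 is equivalent to d = 0.5.
- State that the trial was not sized for UP versus neuropsychological treatment, so that a null result there is read from its confidence interval.
- Minor: say that 123 leaves about 107 at 13% withdrawal, not 108.

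The cost is a less favourable power statement if the arm-by-arm contrast is chosen. Conduct and analysis are unchanged.
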